## Abstract

**Introduction:**

Antenatal corticosteroid (ACS) regimens have remained unchanged since the initial trials in 1972, with the optimal regimen still undetermined. The WHO ACTION (Antenatal CorticosTeroids for Improving Outcomes in preterm Newborns)-III trial is a three-arm individually randomised double-blind trial evaluating the efficacy and safety of two different ACS dosing regimens (currently used and lower-dose ACS regimens vs placebo) in women with a high probability of having a late preterm birth. This study protocol nested within this trial aims to evaluate the pharmacokinetics (PK) and pharmacodynamics (PD) effects of two different ACS dosing regimens in pregnant women in the late preterm period (34–36 weeks) to help inform an optimal dosing regimen.

**Methods and analysis:**

The study will be conducted in two of the five countries participating in the WHO ACTION-III trial—India (Delhi, Belagavi) and Nigeria (Ibadan and Ile-Ife). We will use a population PK approach using sparse sampling to study the PK effects of the two ACS regimens, that is, 6 mg dexamethasone phosphate (DEXp) or 2 mg betamethasone phosphate (BETp), administered intramuscularly every 12 hours for a maximum of four doses or till birth, whichever is earlier, compared with placebo. We will also ascertain the fetal–maternal ratio of DEXp and BETp at birth.

Maternal venous blood samples will be collected at 0, 1–4 hours, 8–12 hours after the first dose, and at 24–36 hours, 48–60 hours, 72–96 hours after the last dose, and immediately after birth, along with cord blood. Concentrations of DEXp and BETp will be measured at set time points using a validated liquid chromatography mass spectroscopy assay. PD parameters measured will include total and differential white blood cell count (by automated analysers using electrical impedance), plasma glucose (hexokinase method) and serum cortisol (using a validated electrochemiluminescence immunoassay), at predefined time points. PK models will be developed for each drug using non-linear mixed effects methods. Optimal dosing will be investigated using Monte Carlo simulations.

**Ethics and dissemination:**

The study has been approved by the WHO Ethics Review Committee and the site-specific ethics committees of the participating leading institutions. Written informed consent will be obtained from all participants. The study results will be published in a peer-reviewed journal and presented at scientific conferences.

**Trial registration number:**

ISRCTN11434567.

STRENGTHS AND LIMITATIONS OF THIS STUDYThis is the first study designed to provide in vivo data on pharmacokinetics (PK) and pharmacodynamics (PD) parameters of two different antenatal corticosteroid (ACS) regimens (the dose currently recommended in early preterm period and a lower dose) among pregnant women in the late preterm period (34–36 weeks of gestation).The study will also ascertain the maternal–fetal ratios of ACS at birth with these two regimens.The study includes a diverse population of pregnant women from South Asia (India) and Africa (Nigeria).Genetic differences among women that could impact the PK or PD of antenatal steroids, as well as variations in placental metabolism that may influence cord blood levels, have not been considered.

## Introduction

 High quality evidence supports the use of antenatal corticosteroid (ACS) for early preterm births (less than 34 weeks gestation),^1 2^ but the recommendations and therefore, the use of ACS in the late preterm period (34–36 weeks gestation) varies globally, given lack of unequivocal benefit–risk balance in this population.^3^,^5^ When ACS is administered to the mother and crosses the placenta into the fetal circulation, all fetal organ systems are exposed to steroids. Recent studies suggest an increase in the short-term adverse effects like neonatal hypoglycaemia^6^ and increased risk of infection in newborns extending into the first year after birth.^7 8^ Longer-term follow-up studies suggest a potential association between steroid exposure in utero and neurocognitive delays or behavioural difficulties in children,^9 10^ as well as potential links with adverse long-term health outcomes.^11^ Despite the fact, ACS, which has multiple widespread biological effects, has not been evaluated for the optimal choice of steroid salt, dose or duration of treatment despite being in use for over 50 years.^12^ Differences in the steroid base, salt, total dose and the dosing interval result in varying levels and duration of steroid exposure for the fetus and thereby differing benefit–risk balances; yet dose-ranging trials to evaluate safety and identify an optimal dosing regimen have never been performed.

Recent animal studies suggest that lung maturational changes can be affected at much lower doses of ACS than those conventionally used in clinical practice,^13^ and while studies on systemic ACS use for different clinical conditions in adults suggest that the risk of adverse effects is proportional to the corticosteroids dose,^14^ there are no studies evaluating a dose–response relationship between different ACS dose regimens and newborn outcomes. The recent BETADOSE trial that evaluated the effects of a 50% reduction in betamethasone dose on neonatal outcomes did not evaluate the pharmacokinetics (PK) and pharmacodynamics (PD) of the different dose regimens.^15^ The PK and PD effects of various ACS regimens are complex, especially as these drugs are administered to pregnant women to treat their fetuses. This complexity arises from several factors, including maternal PK, placental drug transfer and metabolism and fetal metabolism. Few studies have evaluated the PK and PD effects of ACS in pregnant women and their newborns.^12^

The WHO is currently coordinating the ACTION-III trial, a three-arm individually randomised double-blind trial to evaluate the safety and efficacy of different ACS regimens, that is, the dose currently recommended in the early preterm period (dexamethasone phosphate (DEXp) 6 mg every 12 hourly for a maximum of four doses or till birth, whichever is earlier), and a lower dose (betamethasone phosphate (BETp) 2 mg every 12 hourly, for a maximum of four doses or till birth, whichever is earlier), compared with placebo, among pregnant women in late preterm period (34–36 weeks of gestation).^5^ This ongoing study presents a unique opportunity to evaluate the PK and PD of these different ACS regimens in pregnant women that can be used for future calibration and optimisation of ACS dosing for late preterm births.

The primary objectives of the PK-PD study, nested within the trial above, are: (1) to study the PK of two different ACS regimens: BETp four doses of 2 mg each, administered intramuscularly every 12 hours; and DEXp four doses of 6 mg each, administered intramuscularly every 12 hours in pregnant women in the late preterm period (34 to <37 weeks gestation); (2) to study PD effects (plasma glucose, total and differential white blood cell (WBC) counts and serum cortisol) of the above dosing regimens on pregnant women and (3) to compare the PD parameters in pregnant women receiving the above two regimens to those who do not receive either drug (ie, women receiving placebo). The secondary objectives are to assess the concentrations of ACS in cord blood at birth and determine the fetal-to-maternal ratio when each of the two different regimens is used. Additionally, we will study PD parameters in the cord blood of ACS-treated women and compare these with those obtained from placebo-treated women. Furthermore, these parameters will be compared between the African (Nigerian) and South Asian (Indian) pregnant women.

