## Methods and analyses

### Study setting

The WHO ACTION-III trial is being conducted across seven sites in five countries—Bangladesh, India, Kenya, Nigeria and Pakistan. Of these countries, the PK-PD study will be conducted in two countries—two sites in India (Delhi, Belagavi) and two sites in Nigeria (Ibadan and Ile-Ife). These two countries are selected to ensure diverse representation of South Asian and West African pregnant women, given the possible differences in their characteristics such as body mass index (BMI) and pregnancy weight gain.^16^,^18^ The study hospitals in these settings also had the capacity to meet blood sample processing and storage requirements required for this study.

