### Sample size

In each country (India and Nigeria), complete samples from a minimum of 30 women who receive the active drug to enable association of covariates (country, maternal age (years) weight (kg), maternal height (cm), BMI, gestational age, fetal sex) with PK parameters will be required.^25^ Given that all consenting women may not be able to provide the required samples—due to an estimated 30%–40% delivering within 12 hours of the first ACS dose or withdrawing consent—the sample size for each group has been increased by 60% to account for these potential losses, that is, 50 women per arm (DEXp or BETp or placebo) in each country, that is, 150 women from India and 150 women from Nigerian sites.

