#### Random effect models

The between-subject variability will be estimated for all parameters where feasible. A log-normal parameter variability model or other appropriate parameter variability models will be considered for the PK and PD parameters. For the residual unidentified variability, additive, proportional and a combined additive and proportional error models will be considered.

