#### Covariate model

The subject population is a heterogeneous group of women but with limited age ranges. The broad protocol inclusion and exclusion criteria will create considerable inter-subject variability. Assessment of covariate effects such as race and body weights may be possible under these conditions.

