#### Statistical analysis

Drug-related PK and PD individual parameters (eg, V, CL, ka, Emax, EC50) will be summarised using descriptive statistics. Two-way analysis of variance will be applied to test for between drug differences. The population estimates of PK-PD parameters will be compared using 95% CIs. For the model selection, the χ^2^ test for significance of the change in the maximum likelihood objective function will be used. For the selection of significant covariates, the likelihood ratio test will be applied.

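### With two sites per country, the India–Nigeria comparison cannot be separated from site differences; it should be reported by site, as descriptive, and labelled country rather than race

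*Protocol article*

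**What the plan says.** The between-country comparison is a secondary objective in the Introduction: "Furthermore, these parameters will be compared between the African (Nigerian) and South Asian (Indian) pregnant women". It follows directly on the cord-blood and fetal-to-maternal items.

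Study setting gives "two sites in India (Delhi, Belagavi) and two sites in Nigeria (Ibadan and Ile-Ife").

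Sample size requires, in each country, "complete samples from a minimum of 30 women who receive the active drug to enable association of covariates (country, maternal age (years) weight (kg"), with further covariates listed after these. Country is therefore one of the covariates that the sample size is meant to support.

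On the model, Random effect models says: "The between-subject variability will be estimated for all parameters where feasible". It then describes residual error models. No site or hospital level is named. Statistical analysis adds: "For the selection of significant covariates, the likelihood ratio test will be applied". No significance level is given.

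The label changes from section to section. It is country in Sample size, African (Nigerian) and South Asian (Indian) in the Introduction, and race/ethnicity in the Discussion. Covariate model uses race: "Assessment of covariate effects such as race and body weights may be possible under these conditions".

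**The concern.** Country varies only between sites, and there are four sites. Whatever makes women at one site resemble each other (case mix, injection practice, sample handling, local laboratory) goes straight into the country contrast. A likelihood ratio test in a model with only woman-level and residual variability judges that contrast against variation between women, which is the wrong yardstick if sites differ.

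The article itself gives reasons to expect some site variation. Study procedures refers to sampling schedules that differ by site. Sample collection and processing sends glucose and white cell samples to each hospital's own laboratory.

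At stake is a chance difference between two pairs of sites being reported as a population difference in pharmacokinetics or pharmacodynamics. The word *race* makes this worse. The design cannot separate race from country or from site, and the limitations box says that genetic differences were not considered.

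**Working it through.** **The plan's own figure.** Sample size inflates 30 women for losses, "due to an estimated 30%–40% delivering within 12 hours of the first ACS dose or withdrawing consent", to "50 women per arm (DEXp or BETp or placebo) in each country, that is, 150 women from India and 150 women from Nigerian sites". Dividing by the retained fraction at 40% loss gives 30 / (1 − 0.40) = 50, and 3 × 50 = 150 per country. The stated figure is reproduced. (A literal 60% increase gives 30 × 1.6 = 48, within two women.)

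**Inputs from the article.** Two sites per country; 30 women with complete samples per drug per country, reading the 30 as per drug because it is inflated to 50 per arm; 50 enrolled per arm per country.

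**Inputs assumed, because the article does not give them.**
- An even split between sites: m = 30 / 2 = 15 women per site per drug, or 50 / 2 = 25 per site per arm if every enrolled woman contributes.
- A nominal 5% level.
- A site intraclass correlation (ICC) of 0.01 to 0.10.
- No site term in the model.

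**Formulas.** Design effect = 1 + (m − 1) × ICC. True two-sided error = 2 × [1 − Φ(1.96 / √design effect)].

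| ICC | Design effect, m = 15 | 1.96 / √design effect | True error, m = 15 | Design effect, m = 25 | True error, m = 25 |
|---|---|---|---|---|---|
| 0.01 | 1.14 | 1.836 | 6.6% | 1.24 | 7.8% |
| 0.02 | 1.28 | 1.732 | 8.3% | 1.48 | 10.7% |
| 0.05 | 1.70 | 1.503 | 13.3% | 2.20 | 18.6% |
| 0.10 | 2.40 | 1.265 | 20.6% | 3.40 | 28.8% |

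**Check by simulation.** A Gaussian likelihood ratio test that ignores site (20,000 runs per setting, m = 15) rejects in 7.3%, 9.3%, 14.2% and 22.4% of runs at the same four ICCs. It rejects in 5.6% at ICC 0, so a little of the excess is the small-sample behaviour of the test itself.

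**Sensitivity to the assumptions.**
- ICC 0.005 with m = 15: 5.8%.
- A 1% level with m = 15: 1.6%, 2.3%, 4.8% and 9.6% at ICC 0.01, 0.02, 0.05 and 0.10.
- Four hospital clusters per country of 7 women each (simulation, 5% level): 7.0%, 9.3% and 13.2% at ICC 0.02, 0.05 and 0.10.

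**What a valid test could deliver.** A t-test on the four site means has 2 degrees of freedom and a critical value of 4.30. The standard error of the country difference, in standard deviation (SD) units, is √[ICC + (1 − ICC) / 15], which is 0.292 at ICC 0.02 and 0.337 at ICC 0.05. Power for a 1-SD country difference is then about 46% and 38%. A test that ignores site would show 97%.

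**The case against.** A reader might infer that the plan treats women as independent and that its country test has an 8–21% error rate. The article supports neither.

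- **Independence is inferred from silence.** Naming between-subject and residual variability does not exclude a site term. The article assigns a statistical analysis plan to the study statistician, and that plan is not shown. The absence of a site term is therefore a condition of the calculation.
- **8–21% is not a property of this trial.** It needs an ICC of 0.02 to 0.10, a 5% level and 15 women per site. None of these is stated, and 0.10 is arguably more than modest. The article also refers to hospitals, so there may be more than two clusters per country, which lowers the inflation.
- **The test for the quoted comparison is not specified.** The likelihood ratio test is tied to covariate selection in the model. The sentence on Nigerian and Indian women follows the cord-blood objectives, for which no test is named.
- **Site variation is partly controlled.** Drug and cortisol are assayed in one central laboratory, with procedures, training and log review described under Quality assurance. Weight, height, BMI, age and gestational age are listed covariates, so some case mix would be adjusted for.
- **The planned use is cautious.** The comparison is secondary, covariate assessment is only described as possibly feasible, and no country-specific dose is planned.

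All five stand, and they limit the size of the point. They do not remove its core. An analysis plan can add a site term, but it cannot add sites, and two sites per country leave 2 degrees of freedom. The labelling point needs no ICC at all.

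**Conclusion.** The point holds as a limit of the design and of its wording. Two sites per country cannot separate a country effect from site differences. If no site effect is allowed for, the country test is too liberal: about 6.6%, 8%, 13% and 21% at assumed ICCs of 0.01, 0.02, 0.05 and 0.10, with 15 women per site and a 5% level also assumed. The direction follows from any positive site variance; the size is illustrative. Exposure is greatest for glucose and white cell counts and smaller for drug concentrations and cortisol. The article supports a descriptive country comparison shown by site, and it does not support a claim about race. This is a cheap improvement.

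**What to change.** - Report the four site estimates beside every country contrast.
- State that the country comparison is descriptive, and that it is not a basis for a significance claim or for country-specific simulations.
- Add the confounding of country with site to the limitations. At present the two-country population appears only as a strength.
- Replace *race* in Covariate model and *race/ethnicity* in the Discussion with *country*.

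Do not adopt a rule that claims a country difference whenever it exceeds the difference between sites within a country. With four exchangeable site means and no country effect, that rule makes a false claim about 22% of the time if the contrast must exceed both within-country differences, and about 33% if it must exceed their average. A site term nested in country is an option, but its variance would be poorly estimated from four sites, so it does not replace reporting by site.

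Cost: wording and a few table columns, using data already recorded. The downside is that no confirmatory statement about a country difference can be made.

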## Methods and analyses

### Study setting

The WHO ACTION-III trial is being conducted across seven sites in five countries—Bangladesh, India, Kenya, Nigeria and Pakistan. Of these countries, the PK-PD study will be conducted in two countries—two sites in India (Delhi, Belagavi) and two sites in Nigeria (Ibadan and Ile-Ife). These two countries are selected to ensure diverse representation of South Asian and West African pregnant women, given the possible differences in their characteristics such as body mass index (BMI) and pregnancy weight gain.^16^,^18^ The study hospitals in these settings also had the capacity to meet blood sample processing and storage requirements required for this study.

### Study design

The PK-PD study will be nested within the ACTION-III trial (figure 1). The ACTION-III trial enrols women with singleton or multiple pregnancy at 34 weeks 0 days to 36 weeks 5 days of gestation, with at least one live foetus, and a high probability of late preterm birth defined as birth expected between 12 hours and 7 days after randomisation. Women with clinical suspicion or evidence of clinical chorioamnionitis or severe infection, those having received any systemic corticosteroid outside of trial in the previous 2 weeks, no ultrasound assessment of gestational age, major or lethal congenital fetal anomaly, participating in another clinical trial, or having previously participated in any ACTION trial or having any contraindication to corticosteroids are excluded.^5^ Women consenting to participate in the ACTION-III trial are randomised in a 1:1:1 ratio to receive the investigational medicinal product (IMP), which could be any one of the three treatments as follows: (1) DEXp 6 mg intramuscularly 12 hourly for four doses (currently recommended dose) or (2) BETp 2 mg intramuscularly 12 hourly for four doses (lower dose) or (3) placebo. A single course of IMP is administered every 12 hours, to a total of four doses or until birth occurs, whichever occurs first. Enrolment into the PK-PD study: all women randomised into the ACTION-III trial at the selected participating hospitals will be assessed for eligibility for the PK-PD study, and if eligible (criteria listed below), will be enrolled in the PK-PD study following a written, informed consent.

**Figure 1 F1:**
[figure not shown]
PK-PD study flow chart. ACTION, Antenatal CorticosTeroids for Improving Outcomes in preterm Newborns; ACS, antenatal corticosteroid; PD, pharmacodynamics; PK, pharmacokinetics.

### Population PK approach with sparse sampling

The study will use a population PK approach to describe the PK of BETp and DEXp^19^,^21^ in pregnant women in the late preterm period. Population PK modelling approaches rely on data from multiple individuals and often use pooled data from multiple patients, sampled at pragmatic intervals (sparse sampling). This approach is generally used to analyse clinical data collected in a setting where intense sampling (which requires multiple blood draws to obtain a full concentration/response time plot for every individual subject) is not practical. This sparse sampling approach has been used to study the PK of antiretrovirals in pregnancy, as well as in trials for paediatric medicines.^22^,^24^

### Study period

The study is expected to run over a period of 12 months, starting in the third/fourth quarter of 2024. Each enrolled participant will be part of the study for a maximum period of 132 hours after enrolment, beginning an hour prior to the first dose of IMP, up to 96 hours after the last dose. During this study period, blood samples for the measurement of PK and PD parameters from the woman will be drawn at prespecified time points described below. Cord blood will also be collected at birth.

### Study population

The inclusion criteria for the PK-PD study are aligned with those of the main ACTION-III trial, that is, pregnant women in the late preterm period (34–36 weeks gestation) who are eligible for and have been randomised in the ACTION-III trial (see online supplemental file 1, appendix panel 1 for ACTION-III trial eligibility criteria). The exclusion criteria for the PK-PD study are severe anaemia (haemoglobin (Hb) <7 mg/dL; based on the latest available Hb value from the third trimester to the current admission) or having received blood/blood product transfusion in 7 days prior to enrolment in the ACTION-III study.

Consecutive women enrolled and randomised into the ACTION-III trial will be approached during the study period and assessed for eligibility for the PK-PD study. Eligible women will be enrolled in the PK-PD study following written informed consent. The first (baseline) blood sample for the PK-PD study will be drawn before administering the first dose of IMP (DEXp or BETp or placebo) in the ACTION-III trial (figure 1).

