### Study procedures

Serial maternal blood samples will be collected starting before the administration of the first dose of IMP up to 96 hours after the last dose, through a dedicated indwelling cannula or by venipuncture. A cord blood sample will also be collected at birth. The sampling schedule is provided in table 1. All study sites will collect the samples at time points within the sampling time window depicted in table 1 (see online supplemental appendix table 1 for site-specific schedules). The sampling time points for the PK and PD analysis are indicated in table 1.

**Table 1 T1:** Blood sampling schedule

Sample number	Sampling time point	Maternal PK (BETp and DEXp)	Maternal PD (cortisol, glucose, WBC counts)	Cord PK+PD
1	*Baseline (−0.5 hours to 0 hours)*	√	√	
2	1–4 hours post first dose	√	√	
3	8–12 hours post first dose	√	√	
X*	At birth	√	–	√
4	24–36 hours after the last dose†	√	√	
5	48–60 hours after the last dose†		√	
6	72–96 hours after the last dose†		√	

PD parameters include serum cortisol, plasma glucose, total and differential WBC count (neutrophils, basophils and lymphocytes).

Windows for all draws ±30 min, except sample 6. Sample 6 to be drawn as close as possible to the stated time point for the site, otherwise at the point of discharge.

* Birth can happen at any time therefore, birth sample is not numbered sequentially and is labelled as X.

† Regardless of the time of birth.

BETp, betamethasone phosphate; DEXp, dexamethasone phosphate; PD, pharmacodynamics; PK, pharmacokinetics; WBC, white blood cell.

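### The severe-anaemia exclusion is printed as Hb <7 mg/dL, an impossible value that read literally excludes no one; most likely a unit misprint to reconcile with the full protocol

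*Protocol article*

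**What the plan says.** The Study population section of the protocol article sets the PK-PD study's own exclusions, in addition to the entry conditions of the main trial. There are two. The first is "severe anaemia (haemoglobin (Hb) <7 mg/dL; based on the latest available Hb value from the third trimester to the current admission". The second, in the same sentence, is "or having received blood/blood product transfusion in 7 days prior to enrolment in the ACTION-III study".

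This is the only haemoglobin threshold in the article. The Study design section summarises the exclusions of the main ACTION-III trial: suspected or evident chorioamnionitis or severe infection, recent systemic steroids, no ultrasound dating, major fetal anomaly, other trial participation, and contraindication to corticosteroids. Anaemia and haemoglobin are not among them.

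Women who pass these criteria enter a programme of repeated sampling. The Study procedures section opens with this statement: "Serial maternal blood samples will be collected starting before the administration of the first dose of IMP up to 96 hours after the last dose". Table 1 lists six numbered maternal samples plus one at birth.

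**The concern.** The sentence names a condition, severe anaemia, and then defines it by a number that cannot identify it. Haemoglobin in a living patient is a matter of whole grams per decilitre, and the printed limit is seven thousandths of one gram per decilitre. The label and the threshold cannot both be right.

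This is an eligibility limit in the methods, to be compared with a recorded laboratory value, and not a figure in background text. Followed to the letter, it disables one of the two exclusions that belong to the PK-PD study. The transfusion exclusion does not fill the gap, because it does not identify an anaemic woman who has not been transfused. The article gives no reason for the haemoglobin criterion. Sparing anaemic women repeated blood draws is a plausible purpose, but that is an inference.

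**Working it through.** The check is a unit conversion. No sample-size, power or error-rate calculation bears on it, and the plan derives no other figure from this value.

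**Inputs**
- Printed threshold: 7 mg/dL (protocol article, Study population).
- Sampling load, for context only: samples 1 to 6 and X (Study procedures, Table 1), and a 4 mL blood sample for the steroid assay (Sample collection and processing).
- Intended threshold: not stated in any other form. A range of 6 to 10 g/dL is assumed below, only to test how far the conclusion depends on the exact cut-off.

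**Step 1. Convert the printed value.**
7 mg/dL ÷ 1000 = 0.007 g/dL. Multiplying by 10 gives 0.07 g/L. No enrolled woman could have a haemoglobin below this, so the set excluded by the criterion as printed is empty.

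**Step 2. Size of the discrepancy if only the prefix is wrong.**
With the digit 7 kept and g/dL as the unit, the threshold is 7 × 1000 = 7000 mg/dL. Ratio to the printed value: 7000 ÷ 7 = 1000.

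**Step 3. Dependence on the assumed cut-off.**
Ratio = (cut-off in g/dL × 1000) ÷ 7.

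| Assumed cut-off (g/dL) | Ratio to printed value |
|---|---|
| 6 | 857 |
| 7 | 1000 |
| 8 | 1143 |
| 10 | 1429 |

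The printed value is about three orders of magnitude too low throughout. That it is impossible does not depend on the cut-off at all.

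**Step 4. Look for a correcting statement.**
The main-trial exclusions under Study design contain no anaemia criterion. The supplementary panel cited under Study population is described as holding the ACTION-III eligibility criteria, and it is not shown. Nothing in the text at hand restates or overrides the limit.

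**Context: what the criterion gates.**
Six numbered maternal samples + one at birth = up to 7 draws. The drug assay applies to samples 1, 2, 3, 4 and X, so 5 draws. At 4 mL each this is 5 × 4 = 20 mL for the steroid assay alone. These figures describe the study that the criterion controls entry to; they play no part in showing that the unit is wrong.

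**The case against.** The strongest reply is that this is a one-letter slip that every clinical reader will correct. The words severe anaemia stand directly before the number, so no site would take 0.007 g/dL at face value. This objection stands as to consequence: the practical effect is probably small. It does not remove the error from the text.

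A second reply is that a journal article condenses a fuller protocol, and a misprint in the article does not show an error in the operating documents. That is right. The Data collection and management section mentions paper case report forms and a validation system, but does not say that either carries a haemoglobin limit or its unit. A reader might infer that sites and range checks are applying the wrong unit; the documents do not support that. The reply does not dispose of the point, however, because the article states the threshold wrongly and does not merely leave it out.

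A third reply is that the intended unit is nowhere stated, so declaring it to be g/dL assumes that the digit is right. This also stands in part. The label makes g/dL the evident reading, but confirmation has to come from the approved full protocol.

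**Conclusion.** The haemoglobin exclusion is wrong as printed. At 7 mg/dL, or 0.007 g/dL, it is physiologically impossible, contradicts its own label, and read literally excludes no one. It is most likely mg printed for g. The factor of exactly 1000 rests on the assumption that the digit 7 is correct; over assumed cut-offs of 6 to 10 g/dL the factor is about 860 to 1430.

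Two stronger readings should be resisted. One is that anaemic women are in fact being enrolled, or that none is being screened out: the empty exclusion describes the literal text, and nothing shown describes what sites do. The other is that a stated safeguard against blood loss has failed: the article never gives the criterion that purpose. The transfusion exclusion is unaffected, and the sample size, the modelling and the planned comparisons do not use this value. The point is a correction to an operative eligibility limit, worth making because it costs so little, and not a defect in what the study can conclude.

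**What to change.** 1. Compare the printed threshold and unit with the approved full protocol, and reconcile them. The evident intended unit is g/dL, but the source document should settle both the number and the unit.
2. Correct the sentence under Study population accordingly.
3. Confirm that the eligibility form, and any database check on haemoglobin, carry the same unit as the corrected text.

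The first two steps cost one unit correction in the text. The third is a short look at existing forms and settings. If they already carry the right unit, nothing further is needed. If any repeats the misprint, correct it and review the eligibility of women already screened against it. The sample size and the analysis do not change.
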